The **second screening visit** (study visit 2) takes place two to four weeks before the first planned injection. This visit will include review of all laboratory results. At this visit the study nurse confirms that the volunteer fulfils all the inclusion criteria, including laboratory results, makes an abbreviated risk assessment and a brief summary of the study design. Reassurance has to be made that the study volunteer fully understands the concept of the study. The results of the screening investigations will be reviewed and volunteers who are still eligible and willing will be asked to donate blood samples for baseline immunogenicity and complete part 2 of the Informed consent (*Appendix ii/iv, CRF 4-II*). Volunteers will also be reminded that they are free to end all obligations in the study whenever they wish and that a premature termination will not have any negative influence in future contacts with the clinic. If no contraindications are revealed volunteer will be asked to donate blood for first baseline immunogenicity tests.

The volunteer will then be randomized into one of the study arms. At randomization a total of sixty sealed plain envelopes containing an equal number of assignments to groups I, II and IIIa & IIIb, will be prepared and put in the box. Group numbers refer to the immunization schedule.

The study Pharmacist will take the prepared envelopes and put them in the box that is kept under lock. Volunteers accepted into the study will be randomized by a Pharmacist through CRF7-I, by selecting the next consecutive envelope containing the vaccine or placebo assignment in accordance with the generated randomization list. This will be documented in CRF 7-II.

The Pharmacist will then inform the Study Nurse at the clinic of the randomization group of the volunteer (ID or IM) on a copy of CRF 7-I, including a number of the envelope, but will not inform on whether this is vaccine or placebo. The Study Nurse will record the envelope number and the IM/ID assignment into a Register book, the medical record file (source document), as well as the outer cover of the volunteer's file.

The pharmacist will then deliver to the nurse the appropriate vaccine/placebo that corresponds to the assigned group.

Recruitment of volunteers will be staggered so that a maximum of 3 volunteers per week will enter the trial during the first 5 weeks.

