### **Cellular responses**

The assessment of primary cellular responses will be achieved by determining the following HIV-1 specific cellular immune responses:

- CD8 and CD4 T helper cell responses
  - IFN- $\gamma$  ELISPOT and Interleukin-2 assay (on stored Peripheral Blood Mononuclear Cells (PBMC's)), including determination of cross clade responses, using pools of overlapping peptides representing env, gag and pol proteins
  - Intracellular cytokine staining (ICS) for IFN- $\gamma$  and Interleukin-2 (IL-2) (ref 27) using the same peptide pools as in the ELISPOT and testing both for CD8 and CD4 T cell responses
- CD4 T helper cell responses
  - Lymphocyte proliferation assay (LPA) to the immunizing antigens and mitogens on fresh PBMC's
    - Standard assay: measurement of proliferation by uptake of  $^3\text{H}$ -thymidine
    - New assay: whole blood flow-cytometric assay (FASCIA=Flow-cytometric Assay of Specific Cell-mediated Immune response in Activated whole blood) developed at SMI. Both CD4 and CD8 T cell responses can be demonstrated by this method.
- CD8 T cell response
  - Cytotoxic T lymphocytes (CTL) by chromium release assay

Interferon-gamma Enzyme-linked immunospot (ELISPOT) will be used as a standard assay to monitor HIV cellular immune response in vaccinated individuals and will be performed on fresh PBMC's. These procedures will be validated prior to the trial. Individuals with <50 SFC/million PBMCs will be regarded as non-responders. If the average value of sample wells is >4 times the

background (medium only) and >55 SFC/million PBMCs the individuals will be regarded as responders.

A new whole blood flow-cytometric assay (FASCIA=Flow-cytometric Assay of Specific Cell-mediated Immune Response in Activated whole blood) developed at SMI will also be performed later on stored PBMCs. Both CD4 and CD8 T cell responses can be demonstrated by this method. Quality control and exchange of specimens with international laboratories will be performed.

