### **STATISTICAL CONSIDERATIONS**

By the end of this study 60 volunteers will have been exposed to DNA or placebo as well as MVA or saline placebo and described in the quantitative and qualitative immunogenicity and safety evaluation.

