#### *The primary end-points are:*

1. The safety of immunization with the seven DNA plasmids carrying HIV-1 genes as assessed by clinical signs, and standard biochemical/haematological laboratory tests where any worsening of the severity grade will be considered for causality by the vaccine

2. A qualitative and quantitative evaluation of the magnitude and quality of humoral (neutralizing and binding antibodies, by serology) as well as cellular (cytotoxic T-cell, IFN-gamma by ELISPOT, T-cell proliferation (Fascia) and intracellular cytokines by flow cytometry) immune responses as elicited by the different schedules of immunization

The alternative routes of immunization (im and id with the Bioject device) will be evaluated for adverse events by assessing local (pain, cutaneous including induration), general (fever, chills, headache, nausea, vomiting, malaise, myalgia) and other unsolicited adverse events within 7 days. Any grade 3 or 4 event will be taken as an indication that the arm is less tolerable

*The secondary endpoints are:*

1. A qualitative and quantitative assessment on the presence of necessary infrastructure and human capacity to conduct HIV-related vaccine studies at MUHAS.

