### **Immunogenicity Data**

Immunogenicity endpoints will be compared formally at week 0, 10 and 12, according to study dosing group. Binary endpoints will be compared using Fischer's exact test. Continuous endpoints will be compared using 2-sample t-tests or non-parametric equivalents as appropriate to the data.

Immunogenicity of the candidate vaccine will be determined based on comparisons between study treatment arms. Associations between immunogenic endpoints will be assessed using multivariate regression models.

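### The second primary objective rests on six unranked immunogenicity read-outs compared at three weeks with no lead test, so its error rate is uncontrolled, and the named weeks all precede the MVA boosts

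*Protocol*

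**What the plan says.** Determining immunogenicity is the second of two primary objectives (Protocol, Primary objectives). The matching primary end-point is "A qualitative and quantitative evaluation of the magnitude and quality of humoral (neutralizing and binding antibodies, by serology) as well as cellular" responses, the cellular part being "cytotoxic T-cell, IFN-gamma by ELISPOT, T-cell proliferation (Fascia) and intracellular cytokines by flow cytometry". That makes six read-outs, two humoral and four cellular, with no order among them. Some divide further: the ELISPOT is run "using pools of overlapping peptides representing env, gag and pol proteins", and the antibody section adds two binding methods and neutralization against three subtypes.

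The section Immunogenicity Data then fixes the analysis: "Immunogenicity endpoints will be compared formally at week 0, 10 and 12, according to study dosing group". Binary endpoints get Fisher's exact test, and continuous ones a t-test or a non-parametric equivalent. The same section says: "Immunogenicity of the candidate vaccine will be determined based on comparisons between study treatment arms". The arms come from "assignments to groups I, II and IIIa & IIIb", with 20, 20, 10 and 10 volunteers. The protocol does not say which pairs are compared or whether IIIa and IIIb are pooled, and it states no significance level for these tests.

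One assay is given some prominence. Under Cellular responses, the interferon-gamma ELISPOT "will be used as a standard assay to monitor HIV cellular immune response in vaccinated individuals", and responder cut-offs are given for it.

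**The concern.** When many comparisons are formal, equal in rank and together decide a primary objective, no one comparison answers the question and no error rate attaches to the answer. The choice of which result to stress can be made after the data are seen. This is more than detail that a protocol may leave to an analysis plan. The protocol itself fixes what is primary, when it is tested and what the conclusion is drawn from, and leaves out the deciding comparison.

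Two kinds of claim are exposed: that the regimen is immunogenic on some read-out, and that i.m. and i.d. priming differ. There is a second problem with the same passage. The objective concerns the DNA-MVA prime-boost regimen, but the weeks named for formal comparison do not reach the boost.

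**Working it through.** The protocol gives no alpha, power or family-wise rate, so there is no figure of its own to reproduce. The check asks how large the false-positive risk could be, and under which readings.

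**Inputs from the protocol**
- Read-outs: 6. By default neutralization is run on the last serum taken two weeks after vaccination, and on earlier samples only if that one is of interest. It may therefore be absent at the named weeks, which leaves 5.
- Weeks: 0, 10 and 12. Week 0 is baseline. The visit schedule goes from week 8 to week 12, so week 10 has no visit. Two post-baseline weeks is the reading at face value; one (week 12) is the reading that the schedule supports.
- Arm pairs: 3 if placebo is pooled (20/20/20), 1 if only i.m. versus i.d. is considered.

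**Assumptions**
- Two-sided 0.05 per test.
- Any significant comparison counts as positive.
- No true difference between arms.
- Correlation 0.5 between weeks, and 0 to 0.5 between read-outs.

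**Upper guide: independent tests, 1 - 0.95^m**
- m = 6 x 1 x 1 = 6: 26%
- m = 6 x 2 x 1 = 12: 46%
- m = 6 x 1 x 3 = 18: 60%
- m = 6 x 2 x 3 = 36: 84%

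**Simulated t-tests, 20 per arm, pairs sharing arms** (repeat runs differ by a point or two)

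| Reading | Three pairs | i.m. v i.d. only |
|---|---|---|
| 6 read-outs, two post-baseline weeks | 65-76% | 35-44% |
| 6 read-outs, week 12 only | 43-53% | 21-27% |
| 5 read-outs, week 12 only | 39-48% | 18-23% |

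The higher figure in each cell is for uncorrelated read-outs. With correlation 0.9 throughout, six read-outs and three pairs, the risk is 33% for two weeks and 25% for week 12.

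**If every endpoint is binary and tested by Fisher's test.** The exact size of one 20 v 20 test is 0.2% at a 5% response rate in both arms, 1.2% at 10% and 2.4% at 40%. Over six read-outs, three weeks and three pairs, the simulated family-wise rate is about 7-8% at 5% response, 36-44% at 10% and 52-68% at 40% (correlation 0.7 down to 0).

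**Timing.** Placed beside the immunization schedule, weeks 0, 10 and 12 all come before the MVA injections at weeks 36 and 80. At week 12 blood is drawn before the third DNA injection, so that sample reflects two DNA doses only.

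**What one named test would give.** Exact Fisher test, 40 vaccine v 20 placebo. Power is the sum, over all tables with p <= 0.05, of Bin(a; 40, p1) x Bin(b; 20, p2). With 92% responders (the Swedish trial quoted in the protocol) against an assumed 5% in placebo, power is above 99.9%. At 50% against 5% it is 97.6%. The actual false-positive risk is 1.5% at 5% response in both groups and 2.8% at 10%.

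**The case against.** The strongest reply is that the protocol states no decision rule at all. It does not say that one small p-value suffices, and it gives no alpha. The end-point is framed as an evaluation of magnitude and quality, in a 60-person phase I/II study whose statistical section opens descriptively: "By the end of this study 60 volunteers will have been exposed to DNA or placebo as well as MVA or saline placebo". Alpha, the list of contrasts and any adjustment commonly sit in an analysis plan, which is not at hand. ELISPOT is already singled out as the standard assay.

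Much of this stands. The any-significant-result rule is an assumption, and so is 0.05. A reader might infer that a trial with no effect would more often than not show a significant result. The documents do not support that as a general statement: it holds for continuous read-outs at two weeks over three pairs, but is borderline or fails at week 12 alone, fails for i.m. versus i.d. alone, and fails clearly for responder endpoints at low response rates. Nor would an i.m. versus i.d. difference be expected by chance, since 18-44% is below half. It would also be wrong to say that the plan cannot tell an active vaccine from an inactive one. Multiplicity raises false positives; it does not remove the ability to see a large effect.

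What does not stand is the appeal to a descriptive purpose. The protocol calls the end-point primary, calls the comparisons formal and draws the determination from them. Calling ELISPOT the standard monitoring assay does not make it the deciding endpoint, and no visit or arm pair is attached to it.

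**Conclusion.** The point holds in a limited form. Six read-outs are jointly primary, they are compared formally at three weeks, and no read-out, visit or pair leads, so the second primary objective has no controlled error rate. How much that matters depends on how the comparisons would be used, which the protocol leaves open. Most readings checked carry a risk several times 5%; the exception is all-binary endpoints with low response rates. An adjustment may exist in an analysis plan not seen here, but it would not settle which comparison is primary.

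The timing defect needs no assumption. None of the named weeks follows an MVA injection and one has no visit, so the formal comparisons as written cannot answer the prime-boost question. The section needs rewriting for that reason alone, and the lead comparison can be named at the same time.

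**What to change.** In the primary end-points list and in Immunogenicity Data, name one lead comparison. A workable example is IFN-gamma ELISPOT responder status, arms I+II (n=40) versus pooled IIIa+IIIb (n=20), at week 82, two weeks after the second MVA injection. By the protocol's own account that injection is still to come, so the choice can be fixed before those data exist. State alpha and sidedness. Follow in fixed sequence with i.m. versus i.d. on the same endpoint.

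Two items must be settled with it:
- The responder definition leaves values from 50 to 55 SFC per million unclassified, as well as values above 55 that do not exceed four times background. Close both gaps.
- The second MVA injection depends on fresh consent, so some volunteers may have no week 82 sample. Say how they count under the intention-to-treat principle.

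Drop the formal week 0 test, remove or reconcile week 10, and report all other assays, peptide pools and visits as supportive estimates with confidence intervals.

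The change is to wording in two places, with no extra samples or assays. The price is that the other five read-outs can no longer carry a primary claim.

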Safety and Immunogenicity will be assessed at 2 weeks, 1 month, 2 months and 6 months post 2nd MVA.

Between the 1st and 2nd MVA/Placebo vaccinations consenting volunteers will attend the clinic at 8 weeks intervals with a standard follow up. Whenever appropriate, volunteers will also be invited to meetings with the investigators and representatives of the Community Advisory Board aimed at emphasizing low risk behavior towards HIV and AIDS as well as giving updates on matters relating to HIV vaccine trials and HIV and AIDS in general. It will also be an opportunity to maintain contacts with the volunteers and enable the volunteers to share experiences on being in the trial.

**Week 76 (study visit 17)**, this visit will be held four weeks before the 2nd MVA/placebo vaccination, for those who would have given consent during visit 16. Blood will be donated for ELISA HIV testing and for HIV DNA or RNA PCR for those found to have HIV antibodies by ELISA in order to determine if seropositivity is due to HIV acquisition or is a result of candidate HIV vaccine immunogenicity.

**Week 78 (study visit 18)**, this visit will be held two weeks before 2nd MVA vaccination. Volunteers will be given their HIV test results, and those found HIV negative will be invited for 2nd MVA at visit 19. Abreviated risk assessment and appropriate counseling will be conducted

**Week 80 (study visit 19)**, the visit for the second MVA injection of the study vaccine, is conducted by both the study nurse and the study doctor. Before injection the diaries over events after the last injection will be discussed with the study volunteers and an abbreviated risk assessment and risk behaviour counseling will be performed.

Urine for pregnancy test will be performed on female volunteers .

Enough time has to be planned for the visit so that all questions from the volunteers about the study can be answered or reflected upon. Blood will be donated for immunogenicity. The MVA injection is then given and the visit is documented in study form CRF 8-II. Again volunteers will be observed for 30 minutes following injection and new diaries over events for 7 days will be issued.

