## **Immunizations**

### ***Immunization schedule***

While DNA immunizations will be performed at weeks 0, 4 and 12. 1st MVA will be given at weeks 36 and the 2nd MVA will be given at week 80. The immunization schedule is summarized below:

| Weeks                | -4-8 | -2-4 | 0    | 2 | 4    | 6 | 8 | 12   | 14 | 16 | 36    | 38 | 40 | 44 | 60 | 64     | 76 | 78 | 80    | 82 | 84 | 88 | 104 | 106    |
|----------------------|------|------|------|---|------|---|---|------|----|----|-------|----|----|----|----|--------|----|----|-------|----|----|----|-----|--------|
| Visits               | 1    | 2    | 3    | 4 | 5    | 6 | 7 | 8    | 9  | 10 | 11    | 12 | 13 | 14 | 15 | 16     | 17 | 18 | 19    | 20 | 21 | 22 | 23  | 24     |
| Type of immunization |      |      | DNA1 |   | DNA2 |   |   | DNA3 |    |    | MVA 1 |    |    |    |    | EXIT 1 |    |    | MVA 2 |    |    |    |     | EXIT 2 |

| Arm         | Volunteers | DNA immunization                  | MVA boost               |
|-------------|------------|-----------------------------------|-------------------------|
| I    | 20         | DNA intramuscularly by Bioject    | MVA 10  i.m |
| II   | 20         | DNA id by Bioject                 | MVA 10  i.m |
| IIIa | 10         | Saline intramuscularly by Bioject | Saline i.m              |
| IIIb | 10         | Saline id by Bioject              | Saline i.m              |

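### The stated unpaired, single-visit comparisons between arms cannot show what the second MVA injection adds; a within-participant analysis of samples already scheduled can.

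*Protocol*

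**What the plan says.** Under Immunogenicity Data, the protocol states that "Immunogenicity of the candidate vaccine will be determined based on comparisons between study treatment arms". The times are fixed there as well: "Immunogenicity endpoints will be compared formally at week 0, 10 and 12, according to study dosing group". Binary endpoints go to Fisher's exact test, and for the rest "Continuous endpoints will be compared using 2-sample t-tests or non-parametric equivalents as appropriate to the data". A regression model is planned for associations among immunogenicity endpoints. No comparison of a participant with himself or herself appears anywhere in the document.

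The Immunization schedule section has one timetable for all arms: "MVA will be given at weeks 36 and the 2 nd MVA will be given at week 80". Arm I is primed with "DNA intramuscularly by Bioject" and arm II with "DNA id by Bioject". Both then receive MVA at the same dose and route. Arms IIIa and IIIb receive saline at every prime and boost.

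The visit descriptions provide immunogenicity blood at week 80 before the injection, and then "Safety and Immunogenicity will be assessed at 2 weeks, 1 month, 2 months and 6 months post" the second MVA, that is, at weeks 82, 84, 88 and 104.

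**The concern.** The second MVA is a substantial part of the amended trial. It has its own consent step, extension funding, an extra injection and a dedicated series of blood samples. A reader will want to know whether responses rose after it. The analysis text rests the judgement on tests between arms, but no arm receives one active MVA followed by saline, so one boost versus two is never compared by randomisation.

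An analyst who carried the stated tests forward to week 82 or 84 could therefore report a highly significant difference between vaccine and placebo that says nothing about the second injection. The samples that do bear on it would have no planned analysis.

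**Working it through.** The protocol gives no power calculation, so there is no stated figure to reproduce. The check has three steps.

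**1. What each single-visit contrast estimates after week 80**

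| Contrast | What differs between the groups | Second MVA separated? |
|---|---|---|
| I v II (20 v 20) | DNA prime: route and dose | No, both receive it |
| I and II v IIIa and IIIb (40 v 20) | Everything: three DNA doses and two MVA doses v saline | No, mixed with the rest |

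**2. Behaviour of the stated test for responder status** (Fisher's exact, two-sided 5%, exact enumeration)

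*Arm I v arm II*, with the second MVA raising both arms to the same true rate p:

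| p | Rejection probability |
|---|---|
| 41.3% | 0.023 |
| 60% | 0.024 |
| 92% | 0.007 |
| 99% | 0.000 |

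The test stays at its null level whatever the second MVA achieves. The 41.3% is the pooled interim ELISPOT rate of 19/46 after DNA or placebo. The 92% is the 34/37 from the Swedish trial. Both serve only as illustrative rates.

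*Vaccine v placebo*, 40 v 20, placebo rate 0% or 5% (assumed): power is 0.998 to 1.000 at vaccine rates of 60%, 80%, 92% and 99%. A rise from 60% to 92% after week 80 and no rise at all give the same significant result.

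**3. What the scheduled samples can show**

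Let D be the log10 response at week 82 or 84 minus the log10 response at week 80 before the dose. The SD of D is not in the protocol, so 0.3 to 0.7 is assumed, equal in both groups, with no mean change on placebo.

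Paired t-test, n = 40, noncentral t with parameter (mean D / SD) × √40: 80% power at a standardised change of 0.454.

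- SD 0.3: 0.454 × 0.3 = 0.136 log10, or 1.37-fold
- SD 0.5: 0.454 × 0.5 = 0.227 log10, or 1.69-fold
- SD 0.7: 0.454 × 0.7 = 0.318 log10, or 2.08-fold

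With 20% lost or not consenting (n = 32, assumed), the standardised change is 0.511. At SD 0.5 this gives 0.511 × 0.5 = 0.256 log10, or 1.80-fold.

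Mean change in vaccinees compared with mean change on placebo, 40 v 20, parameter (difference / SD) / √(1/40 + 1/20):

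| Rise (log10) | SD | Paired, n = 40 | Change, 40 v 20 |
|---|---|---|---|
| 0.3 | 0.3 | 1.00 | 0.95 |
| 0.3 | 0.5 | 0.96 | 0.58 |
| 0.3 | 0.7 | 0.75 | 0.34 |
| 0.5 | 0.5 | 1.00 | 0.95 |

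Both analyses respond to the second MVA. The paired one is the more sensitive, and the comparison with placebo guards against assay drift.

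Responder status has less room to move. If 92% were still responders at week 80, at most 8% could gain a response. With no losses, exact McNemar needs at least 6 discordant pairs, all gains, for p < 0.05. P(X ≥ 6) for X ~ Binomial(40, 0.08) is 0.097, so power is about 10%. Magnitude should lead.

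**The case against.** The strongest reply is that the trial does not ask this question. The objectives concern the immunogenicity of the whole DNA-MVA regimen, no endpoint names the increment from the second boost, and vaccine versus saline is the valid randomised comparison for the regimen. A supplementary paired analysis could also sit in a statistical analysis plan that is not shown. The first part stands, so the increment can only be a secondary contrast. The second part carries less weight, because the protocol does more than stay silent: it names the basis for the conclusion and the tests, and both are unpaired.

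A reader might infer several stronger things that the protocol does not support:

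- **That no comparison between arms could ever show the effect.** The change from week 80 to weeks 82/84, MVA versus saline, is a comparison between arms and responds to the second MVA. The limitation applies to tests at a single visit, and no change score is named.
- **That comparisons between arms are the exclusive basis.** The text does not say so. It also foresees descriptive evaluation and a regression of associations.
- **That 34/37 responders is what a first MVA alone produces.** The background section reports it for the DNA-MVA combination and does not tie it to one MVA injection.
- **That the primary endpoint's reference to "immune responses as elicited by the different schedules of immunization" is an error because all arms share one timetable.** The randomisation text uses schedule to mean group assignment, so this is loose wording at most.

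It is also fair to say that the paired contrast is not decisive. A rise after week 80 may only restore a response that had waned. Comparing the peak after the first MVA with the peak after the second is confounded by time and by the change of manufacturer described under the supply of MVA.

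**Conclusion.** The point holds in this limited form: none of the stated tests, applied at any single visit, can show what the second MVA adds, although the samples that bear on it are scheduled. That follows from the arm and schedule tables alone and needs no assumption. A related fault in the same section is that all the formal weeks precede both MVA injections, and week 10 is not a visit in the schedule. Adding later weeks would repair the whole-regimen comparison but not this one.

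The gain from a paired analysis, about a 1.7-fold detectable rise with 40 vaccinees, rests on an assumed SD of 0.5 and full participation. The plausible range is 1.4-fold to 2.1-fold, and somewhat wider with losses. This is a worthwhile improvement at almost no cost. It does not undermine the regimen-level objective.

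**What to change.** Add one paragraph to Immunogenicity Data:

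- **Main second-boost analysis:** in arms I and II combined, among those actually given the second MVA (40 less losses and non-consent), the change in log10 response magnitude from week 80 before the dose to weeks 82/84, with a 95% confidence interval. Fix in advance whether week 82, week 84 or their maximum is used.
- **Control:** the same change in placebo recipients, and the difference in change (MVA versus saline) with its 95% confidence interval.
- **Supportive only:** exact McNemar for responder status across week 80, and the peak at weeks 38/40 against the peak at weeks 82/84. Quote power for McNemar only with a stated assumption about waning by week 80.
- **Interpretation:** say that the increment is a secondary, non-randomised contrast, that it may reflect restoration of a waned response, and that the peak comparison is confounded by time and manufacturer.
- **Times:** name the visits after MVA at which the regimen is compared with placebo.

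The cost is a paragraph of text and some programming. No visit, sample or assay is added.
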